**8. Data Management**

8.1 Completion and Transfer of Case Report Forms (CRFs)

- CRFs are to be completed by the physician, and a complete CRF must be filled out for each enrolled case. After completion and review by the investigator, the first copy of the CRF will be transferred to the data manager for data entry and management.

8.2 Data Entry and Modification

- Data entry and management are handled by data managers authorized by Ruijin Hospital, affiliated to Shanghai Jiao Tong University School of Medicine. Data managers will use Epidata software to develop the data entry program for data entry and management. To ensure data accuracy, two data entry personnel will independently perform double data entry and cross-checking.

- For issues identified in the CRFs, the data manager will generate a Data Clarification Form (DCF) and send inquiries to the investigator. The investigator should respond and return the DCF as soon as possible. The data manager will then make, confirm, and update the data modifications based on the investigator’s responses.

8.3 Data Locking

- After all inquiries have been resolved and the database is confirmed to be correct, the data manager will write a data management audit report. In the presence of the principal investigator, statistical analysts, and data management personnel, the analysis dataset will be finalized and reviewed. The locked data is considered archived data, and in principle, no further changes will be made to the archived data files.

**9. Data Statistics and Analysis**

9.1 General Arrangement

- Descriptive statistical analysis will be primarily used in this study, and statistical processing will be conducted using R (v4.1.0) software.

9.2 Analysis Population

- The analysis population includes the full analysis set, the per-protocol set, and the safety analysis set. The total number of enrolled patients, the number in each set, and the number excluded will be recorded, and the dropout cases will be described.

- Full Analysis Set (FAS): Based on the intention-to-treat (ITT) principle, the FAS includes all enrolled patients who have used the study drug at least once, excluding a minimal number of patients who have not used the study drug or have seriously violated the inclusion/exclusion criteria. Efficacy analysis will be performed on all cases that were enrolled and used the drug at least once.

- Per-Protocol Set (PPS): Based on the FAS, the PPS further excludes any protocol-violating patients, including all cases that completed at least 2 cycles (including 2 cycles), complied with the trial protocol, had good medication compliance, did not use prohibited medications during the trial, and completed the contents specified in the CRF. Missing values will not be estimated. Both FAS and PPS will be used for statistical analysis of drug efficacy.

- Safety Analysis Set: Excludes a minimal number of patients who have not used the study drug or have no safety evaluation data from the ITT set. It includes all patients who used the study drug at least once after enrollment and have safety records post-medication. This dataset is used for safety analysis.

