**Study Synopsis**

| **Study title** | A phase 2 pilot study of umbilical cord blood infusion as an adjuvant consolidation therapy in elderly patients with acute myeloid leukemia |
| --- | --- |
| **Indication** | AML consolidation therapy |
| **Objectives** | To assess the efficacy and safety of UCB infusion as an adjuvant consolidation therapy in elderly patients with AML |
| **Study design** | A single-arm, single-center, phase 2 trial |
| **Study center** | Ruijin Hospital affiliated to Shanghai Jiao Tong University  School of Medicine |
| **Participants** | Elderly patients (age ≥ 60 years) with newly diagnosed AML |
| **Study endpoints** | **Primary endpoint**: overall survival (OS)  **Secondary endpoints**: event-free survival (EFS), bone marrow measurable residual disease (MRD), treatment-related adverse events (AEs), and median times to platelet and neutrophil recovery  **Exploratory endpoint**: single-cell RNA sequencing (scRNA-seq) of matched samples collected before and after UCB infusion |
| **Sample size** | 65 elderly patients diagnosed newly with de novo AML were assessed for eligibility and 51 were enrolled. |
| **Inclusion criteria** | 1. Age ≥ 60 years old; 2. Newly diagnosed with de novo AML, examined by bone marrow according to the World Health Organization (WHO) 2022 criteria; 3. Eastern Cooperative Oncology Group (ECOG) performance score 0 to 2; 4. Echocardiography examination of Left Ventricular Ejection Fraction (LVEF) ≥ 50%; 5. Estimated glomerular filtration rate (eGFR) ≥ 60 mL/min, measured using the CKD-EPI formula; 6. Alanine aminotransferase (ALT) ≤ 2.5×upper limit of normal (ULN), aspartate aminotransferase (AST) ≤ 2.5×ULN and total bilirubin ≤ 1.5×ULN; 7. Documented CR after one or two cycles of induction therapies defined according to standard criteria; 8. Inability or unwillingness to undergo allo-HSCT; 9. Signed informed consent before admission to the study. |

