5.2 Study Treatment

Consolidation Therapy:

- Two cycles of 15 mg/m^2^ low dose intravenous decitabine (DAC) over 4h per day for consecutive 5 days (day 1-5), 1.0 g/m^2^ intermediate-dose cytarabine (Ara-C) at q12h for consecutive 2 days (day 6-7), combined with one unit UCB infusion on day 9.

- No immunosuppression was given as prophylaxis for GVHD, unless acute GVHD (aGVHD) was documented or clinically diagnosed.

Selection of UCB:

- High-resolution Human Leukocyte Antigen (HLA) typing for HLA-A, B, and DR loci was performed in all enrolled patients.

- The UCB units were obtained from the cord blood bank at the China Shandong Cord Blood Bank Network if they met the following criteria:

a). Serologically matched of four or five of six HLAs.

b). Contained at least 3 × 10⁷ nucleated cells/kg of recipient body weight before freezing.

Maintenance Therapy:

- Decitabine 15 mg/m² for 5 days, every 28-day cycle.

OR

- Azacitidine 75 mg/m² for 7 days, every 28-day cycle.

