**7. Safety Evaluation**

The investigator is responsible for monitoring the safety of all enrolled subjects and recording any adverse events (AEs) and serious adverse events (SAEs). AEs monitoring began after the first patient enrollment and was monitored continuously until the last follow-up.

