7.2 Definition of Adverse Events (AEs)

Treatment-related AEs, including hematological and non-hematological AEs, were defined as those that occurred from the start of treatment. For pre-existing abnormalities in physical or laboratory examinations, an increase in severity after treatment was also considered as an AE. The investigator should record all AEs in detail, including descriptions and related symptoms, time of occurrence, severity, duration, measures taken, and outcomes.

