7.2.2 Criteria for Determining the Relationship Between AEs and Study Drug

All AEs must be reported in clinical reports, and any discomfort or abnormal changes in objective laboratory indicators during the trial must be recorded accurately, indicating the severity, duration, treatment measures, and outcomes. Clinicians should use a five-category method ("definitely related," "probably related," "possibly unrelated," "definitely unrelated," and "unable to determine") to comprehensively judge the relationship between AE and the study drug. "Definitely related," "probably related," and "unable to determine" are classified as drug adverse reactions. The incidence of AEs is calculated as the sum of these three categories as the numerator and the total number of subjects evaluated for safety as the denominator.

| **Category** | **Criteria** |
| --- | --- |
| Definitely related | The event occurs in a reasonable sequence after drug administration, matches the known reaction type of the suspected drug, improves after discontinuation, and recurs after re-administration. |
| Probably related | The event occurs in a reasonable sequence after drug administration but does not match the known reaction type of the suspected drug; the patient's clinical status or other treatments may also cause the event. |
| Possibly unrelated | The event does not occur in a reasonable sequence after drug administration, does not match the known reaction type of the suspected drug, and the patient's clinical status or other treatments may cause the event. |
| Definitely unrelated | The event does not occur in a reasonable sequence after drug administration, does not match the known reaction type of the suspected drug, the patient's clinical status or other treatments may cause the event, and the event disappears after discontinuing other treatments or improving the disease and reappears after reintroducing other treatments. |
| Unable to determine | The event's occurrence and timing have no clear relationship with drug administration, similar to the drug reaction type, and other concurrent medications may also cause the event. |

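### The adverse-event definition and the causality rule do not separate cord blood from chemotherapy or maintenance, although the synopsis objective is the safety of UCB infusion

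*Protocol*

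**What the plan says.** The Study Synopsis gives the objective as "To assess the efficacy and safety of UCB infusion as an adjuvant consolidation therapy in elderly patients with AML". Section 2.1 instead names the combination of decitabine, cytarabine and UCB.

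In section 5.2, each consolidation cycle has decitabine on days 1-5 and cytarabine on days 6-7, "combined with one unit UCB infusion on day 9". Maintenance with decitabine or azacitidine appears under the same heading. The study-treatment row of the synopsis lists only the two consolidation cycles with UCB.

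Four safety rules apply:

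- **Section 7:** "AEs monitoring began after the first patient enrollment and was monitored continuously until the last follow-up".
- **Section 7.2 (repeated in the synopsis):** "Treatment-related AEs, including hematological and non-hematological AEs, were defined as those that occurred from the start of treatment".
- **Section 7.2.2:** the clinician uses five categories to "comprehensively judge the relationship between AE and the study drug". Definitely related, probably related and unable to determine make up the numerator. All subjects evaluated for safety make up the denominator.
- **Section 9.2:** the safety set requires one use of the study drug and later safety records: "It includes all patients who used the study drug at least once after enrollment and have safety records post-medication".

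Section 7.3.6 lists GVHD of any grade and infusion reactions of grade 3 or higher as AEs of special interest. It gives no denominator of their own.

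**The concern.** The trial has no control arm. The safety data can be related to UCB only through component, timing and exposure, and the rules above use none of the three.

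Sections 7.4 and 7.5 list neutropenia, thrombocytopenia, anemia and infection as common reactions to both chemotherapy drugs. Under section 7.2 each of these is treatment-related whether it starts on day 3 or day 20. Section 7.2.2 refers to the known reactions of the suspected drug but keeps one answer, so the component the clinician suspected is lost.

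The two sections also disagree on what related means: timing alone in 7.2, a clinical judgement in 7.2.2. One event can be treatment-related under the first and definitely unrelated under the second.

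At stake is whether the safety output can speak to the synopsis objective. A smaller matter is whether rates of GVHD and infusion reactions are divided by patients who could have had them.

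**Working it through.** The protocol states no UCB-specific rate and no safety-set size, so there is no figure to reproduce. The check sets the rules side by side and then sizes the denominator effect.

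**1. Separation of components**

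| Rule | Section | Separates UCB from chemotherapy or maintenance? |
| --- | --- | --- |
| Safety-set entry | 9.2 | No; any use of the study drug |
| AE monitoring window | 7 | No; from enrollment to last follow-up |
| Definition of treatment-related | 7.2 | No; timing from the start of treatment |
| Causality | 7.2.2 | No; one answer, study drug undefined |
| Incidence denominator | 7.2.2 | No; all safety-evaluated subjects |
| AEs of special interest | 7.3.6 | By event type only; no at-risk group |

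**2. Timing.** UCB comes on day 9, and 9 − 1 = 8 days (days 1-8) precede it. In the first cycle, an event starting in those days cannot be due to UCB, yet section 7.2 labels it treatment-related. If section 7.2 is read with the monitoring window in section 7, events during maintenance carry the label too. Section 5.2 does not say whether the single unit is given in each cycle or once per patient, so what counts as before UCB in cycle 2 depends on the answer.

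**3. Denominator.** Inputs: N = 51 enrolled (section 15), all taken as dosed; m = number dosed but never infused (not stated, assumed 0 to 8); x = 5 events (assumed).

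Rate on all dosed patients = x/N. Rate on infused patients = x/(N − m). Ratio of the second to the first = N/(N − m).

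| m | Infused | 5 events on 51 | 5 events on infused | Ratio |
| --- | --- | --- | --- | --- |
| 0 | 51 | 9.8% | 9.8% | 1.00 |
| 1 | 50 | 9.8% | 10.0% | 1.02 |
| 3 | 48 | 9.8% | 10.4% | 1.06 |
| 5 | 46 | 9.8% | 10.9% | 1.11 |
| 8 | 43 | 9.8% | 11.6% | 1.19 |

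The largest shift is 11.6 − 9.8 = 1.8 percentage points. The exact 95% interval for 5/51 runs from 3.3% to 21.4%, so the shift is well inside sampling error.

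**4. Can recorded data supply a split?** Largely yes. Section 7.2 requires the time of occurrence of every AE. Sections 5.3 and 5.5 schedule chimerism testing and follow-up by days after UCB, so the infusion date must be known. Component-level causality is different: the protocol never asks for it.

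**The case against.** The strongest reply is that an any-dose safety set is standard and fits section 2.1, which aims at the combination. That stands, and section 9.2 needs no change.

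A reader might infer more than the text supports, on four points:

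- **That chemotherapy toxicity is counted as UCB toxicity.** No section does so. Events are attributed to the study drug or to treatment. The problem arises only when pooled events are read against the synopsis objective.
- **That the AE clock starts with decitabine on day 1.** Section 7 starts monitoring at enrollment, and section 9.2 names no drug. Day 1 is an inference from the schedule.
- **That UCB rates have a wrong denominator.** No UCB-specific rate is defined. The denominator is unsuitable only if the rule in section 7.2.2 is applied to GVHD or infusion reactions and some dosed patients were not infused.
- **That maintenance events are all counted as reactions.** The synopsis leaves maintenance out of study treatment, and section 7.2.2 counts an event only if it falls in one of three categories.

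The UCB-linked signals are also partly covered: GVHD and severe infusion reactions are flagged, and chimerism is timed from infusion.

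It can further be said that subsets and period tables belong in a statistical analysis plan, which is not shown. Their absence alone would not be a fault. But the protocol itself fixes the definition of related, the object of the causality judgement, the numerator and the denominator. A later plan can add tables, but it cannot recover a component judgement that was never collected.

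Finally, UCB follows the last cytarabine day by two days (day 7 to day 9), so cytopenia and infection after UCB stay confounded with chemotherapy. This stands in full and limits what any repair can claim.

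**Conclusion.** The point holds in a limited form. Sections 7.2 and 7.2.2 conflict on what is treatment-related, leave the study drug undefined, and collect no information by component, while the synopsis states an objective about UCB itself. The safety output as planned describes the regimen and does not address that objective.

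The main loss is attribution, and the documents give no figure from which to size it. The denominator effect is secondary: zero if all dosed patients were infused, and at most a factor of 1.19 under the assumed range of 0 to 8 non-infused patients. The 5 events are also an assumption. Changes are worth making because they are cheap and draw largely on recorded data, not because any reported rate has been shown to be wrong.

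**What to change.** Keep the safety set in section 9.2 for the regimen, and then:

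1. Define the study drug, stating whether it covers UCB, consolidation chemotherapy and maintenance, and align the synopsis objective with section 2.1.
2. Reconcile the timing rule in section 7.2 with the causality rule in section 7.2.2. One solution is to call the first treatment-emergent and keep related for the second.
3. Record relationship separately for UCB, consolidation chemotherapy and maintenance. Enrollment has ended, so for events already collected this would be retrospective and should be labelled so.
4. Report GVHD, infusion reactions and chimerism among patients who received UCB, with time counted from infusion, and state how many dosed patients were not infused.
5. Tabulate AEs by recorded onset date: before UCB, after UCB within consolidation, and during maintenance. State whether UCB was given once or in each cycle, so that the periods are unambiguous.
6. State that the period after UCB remains confounded with chemotherapy, so the tables describe UCB toxicity and do not isolate it.

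The cost is a little more tabulation, plus a retrospective causality review if item 3 is applied to existing events. UCB-specific rates may become slightly less favourable.

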9.3 Main Results and Analysis Methods

Clinicopathological characteristics of patients were summarized by utilizing frequencies (%) for categorical variables and medians (range) for continuous variables. Fisher’s exact test was used to compare the associations for categorical variables versus categorical variables. Wilcoxon rank sum test was employed to compare categorical variables versus continuous variables. False discovery rate (FDR) corrected by Benjamini-Hochberg approach was applied to adjust the p value for multiple testing unless otherwise specified. Kaplan–Meier survival curves were utilized to evaluate the probabilities of OS and EFS. Log-rank test was performed to compare the survival curves. Asterisks define significance levels. All statistical tests were two-sided unless otherwise specified. Statistical analyses were carried out using R (v4.1.0) packages.

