2.2 Study Endpoints

2.2.1 Primary Endpoint

- Overall Survival (OS): defined as the time interval from the date of diagnosis to date of death from any cause, with censoring of patients known to be alive upon the last follow-up.

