2.2.3 Exploratory Endpoint

- Single-cell RNA sequencing (scRNA-seq) of matched samples collected before and after UCB infusion.

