3.2 Planned Sample Size

This study is a phase 2 clinical trial using a single-arm, single-stage design method to calculate the sample size. The primary endpoint is the 2-year OS of all enrolled patients. Based on prior knowledge, the 2-year OS with standard chemotherapy is about 50%. Assuming the 2-year OS expectation with UCB treatment is 67%, with P1 = 0.67 (superior) and P0 = 0.50 (inferior), α = 0.05, β = 0.20, and considering a 5% expected dropout rate, the study plans to enroll approximately 52 patients.

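### The trial is sized to test 2-year OS against 50%, but the primary endpoint is elsewhere given without a time point, no stated analysis refers to 50%, and the sidedness conflicts

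*Protocol*

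**What the plan says.** **Primary endpoint.** Section 3.2 reads: "The primary endpoint is the 2-year OS of all enrolled patients". Section 2.2.1, under the primary endpoint heading, reads: "Overall Survival (OS): defined as the time interval from the date of diagnosis to date of death from any cause", with patients alive at last follow-up censored. It gives no landmark and no reference value. The synopsis agrees with section 2.2.1, and section 6.2 repeats the definition.

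**Sizing.** Section 3.2 describes the trial as "using a single-arm, single-stage design method to calculate the sample size". The null rate is the historical figure: "Based on prior knowledge, the 2-year OS with standard chemotherapy is about 50" per cent. The alternative is 0.67, with α = 0.05, β = 0.20 and 5% dropout, giving about 52 patients. Section 3.2 does not say whether α is one- or two-sided.

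**Analysis.** Section 9.1 says: "Descriptive statistical analysis will be primarily used in this study". Section 9.3 lists Fisher's exact test, the Wilcoxon rank-sum test, Kaplan-Meier curves for OS and EFS, and a log-rank test: "Log-rank test was performed to compare the survival curves". It does not say which curves are compared. Tests are two-sided by default. The synopsis repeats this list.

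**Conduct.** Section 15 gives 51 enrolled, enrolment closed on 12 February 2022 and last follow-up on 31 March 2023.

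**The concern.** The sample size rests on one specific question: is the 2-year OS rate above 50%? The analysis sections neither name that quantity nor mention 50%. A Kaplan-Meier curve contains a 24-month estimate, but no time point, confidence limit or success criterion links it to the reference rate. The trial has one arm, so a log-rank test with no reference curve can only compare subgroups of that arm, and such a comparison says nothing about 50%.

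At stake is whether the primary result can be read as positive or negative by a rule fixed in the protocol. With about 51 patients, a 2-year OS in the high 50s would look favourable beside the historical 50% yet be well within chance of it. Near the boundary, the conclusion would also depend on a sidedness that the document leaves in conflict.

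**Working it through.** **Inputs.** P0 = 0.50, P1 = 0.67, α = 0.05, power 0.80, dropout 5%, planned N about 52 (section 3.2); 51 enrolled and the dates (section 15); two-sided default (section 9.3).

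**1. Reproducing about 52, one-sided α (z = 1.645 and 0.842).**
- Variance at P1: (1.645 + 0.842)² × 0.67 × 0.33 / 0.17² = 47.3, so 48; 48/0.95 gives 51.
- Complementary log-log scale, with standard deviation √[(1−p)/(p·ln²p)] = 1.443 at 0.50 and 1.752 at 0.67, and distance ln(0.6931/0.4005) = 0.549: (1.645 × 1.443 + 0.842 × 1.752)² / 0.549² = 49.2, so 50; 50/0.95 gives 53. Rounding only at the end, 49.2/0.95 = 51.8, which is 52.
- Null and alternative variances: (1.645 × 0.5 + 0.842 × 0.470)² / 0.17² = 51.3, so 52 before dropout and 55 after.
- Exact binomial: the first N with power of at least 0.80 is 53, so 56 after dropout.

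**2. The same with two-sided α (z = 1.960).** The corresponding methods, with arcsine and continuity-corrected versions added, give 61 to 72 before dropout and 65 to 76 after. None gives 52. The stated size is therefore that of a one-sided, one-sample test of a landmark rate.

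**3. What the choice of side does at n = 51.** Exact binomial against 0.50, with X the number alive at 2 years:

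| Alive | Rate | One-sided p | Two-sided p | P(X ≥ this number) if the true rate is 0.67 |
|---|---|---|---|---|
| 28 | 54.9% | 0.288 | 0.576 | – |
| 31 | 60.8% | 0.080 | 0.161 | – |
| 32 | 62.7% | 0.046 | 0.092 | 0.788 |
| 33 | 64.7% | 0.024 | 0.049 | 0.695 |

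One-sided success needs 32 alive and two-sided success needs 33. A result of 32 of 51 passes one rule and fails the other. Approximate two-sided power at n = 51 is 0.691 (normal) or 0.733 (log-log scale), so about 70% overall.

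**4. Precision.** The 95% half-width, 1.96 × √[p(1−p)/51], is 0.137 at p = 0.50 and 0.129 at p = 0.67. Results of 28 to 31 alive (55% to 61%) do not reject 50% under either rule.

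**5. The log-log bound with no censoring.** Lower limit = exp(−exp[ln(−ln S) + z × SE]), with SE = √[(1−S)/(51·S)] / |ln S|.
- 32/51: S = 0.627, SE = 0.2315. The limit is 0.506 with z = 1.645 and 0.480 with z = 1.960.
- 31/51: the limit is 0.486 with z = 1.645. The one-sided threshold therefore matches the exact test.
- 33/51: S = 0.647, SE = 0.2376. With z = 1.960 the limit is 0.4998, just short of 0.50, so the interval method also matters at the two-sided boundary.

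**6. Follow-up.** From 12 February 2022 to 31 March 2023 is about 13.5 months. OS runs from diagnosis, so anyone diagnosed after 31 March 2021 and still alive at last follow-up is censored before 2 years. The counts above are then approximate, and the power figures are upper values.

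**The case against.** The strongest reply is that the sections fit together. Sections 2.2.1 and 6.2 define the variable, section 3.2 gives the time point used for sizing, and 2-year OS is a summary of that variable with the same event and origin. Kaplan-Meier estimation yields the 24-month rate, a mainly descriptive analysis does not exclude a one-sample test, and the confidence method and decision rule could sit in a statistical analysis plan that is not at hand.

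Part of this stands. These are not rival clinical outcomes, and a missing interval formula would be no finding. But section 3.2 says in terms that the 2-year rate is the primary endpoint, while the section headed as primary endpoint gives no landmark. Section 9.3 does not defer its methods: it lists them, and none is tied to 50%. The one-sided size against a two-sided default is a conflict within the protocol itself.

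A reader might infer three stronger points that the document does not support:
- **That a log-rank test is invalid in a single arm.** It can compare subgroups, and a one-sample version exists given a reference curve. The defect is that the comparator is not named.
- **That the powered hypothesis will never be tested.** All that can be said is that this protocol states no test of it.
- **That matched data will be analysed with unpaired tests.** Section 2.2.3 lists "Single-cell RNA sequencing (scRNA-seq) of matched samples collected before and after UCB infusion", and section 9.3 says "Wilcoxon rank sum test was employed to compare categorical variables versus continuous variables", but section 9.3 never assigns that test, or Fisher's, to before-and-after comparisons.

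**Conclusion.** The point holds as a contradiction within the protocol and should be corrected before the primary result is interpreted. The primary endpoint is a 2-year rate in one place and an unanchored survival time in others, and no stated analysis compares 2-year OS with the 50% on which the trial is sized. The sample size implies one-sided α = 0.05, whereas the analysis section defaults to two-sided.

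In size, the sidedness moves the exact threshold at n = 51 from 32 to 33 alive and the power from about 0.79 to about 0.69. The absence of a criterion leaves results of roughly 55% to 61% open to a favourable reading that the data would not support. The figures assume 51 analysed patients with known 2-year status, and true rates of 0.50 and 0.67 as the protocol sets them. Censoring before 2 years would lower the power.

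**What to change.** - In the synopsis and section 2.2.1, name one primary endpoint: the 2-year OS rate, with the existing definition of OS as its basis.
- In sections 9.1 and 9.3, make the primary analysis the Kaplan-Meier estimate at 24 months with a log-log (Greenwood) lower confidence bound. Success means that the bound exceeds 50%.
- In sections 3.2 and 9.3, state that this test is one-sided at 0.05, as the sample size implies. Otherwise keep two-sided 0.05 and restate the power with 51 patients as about 70%, recomputed for the exact bound chosen, since 33 of 51 sits on the boundary.
- Say what the log-rank test compares, and label subgroup comparisons exploratory.
- If outcomes were known when the rule was written, disclose it as post hoc.

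The cost is a few lines of text and no new data. Choosing two-sided testing also means reporting the lower power.
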